#### SPACE FOR COPD group-based self-management programme

Participants in the intervention group receive a SPACE for COPD(C) manual and are asked to attend the SPACE for COPD(C) group-based self-management programme usually within 1 month of their baseline appointment. The aim of the SPACE for COPD(C) programme is to support people with COPD in managing day-to-day tasks, minimise symptom burden, provoke health enhancing behaviour change and enhance emotional well-being. The programme is structured around the SPACE for COPD(C) manual, which combines both generic self-management skills and disease-specific tasks. The programme is facilitated by two trained HCPs (eg, physiotherapists, respiratory specialist nurses, occupational therapists and health psychologists) to groups of up to 10 participants and delivered through six 2-hour sessions, over a 5-month period. These sessions will be held at community venues, at times and locations to suit participants of the group to increase retention. Participants are liaised with in regards to preferences on timings and location of the group sessions to increase retention and engagement in the intervention. The content of the programme and accompanying self-management components^15^ are presented in tables 1 and 2. Participants are provided with a contact number for at least one of the facilitators throughout the course of the programme in case they have any further queries/are unable to attend any sessions.

**Table 1 T1:** SPACE for COPD(C) self-management programme session outline

Session 1 (week 1)	Introduction to SPACE for COPD(C)
1	Welcome and introductions
2	Group responsibilities
3	What does it mean to have COPD?
4	What is self-management?
5	How to use the SPACE for COPD(C) manual
6	Goal setting
7	Home activities for next session
8	Summary and close
Session 2 (week 2)	Introducing exercise and managing shortness of breath
1	Welcome back
2	Solution focused goal feedback
3	Managing shortness of breath
4	Introduction to the walking programme
5	Goal setting
6	Activities for next session
7	Summary and close
Session 3 (week 4)	Continuing exercise and saving energy
1	Welcome back
2	Solution focused goal feedback
3	Saving your energy
4	Strength training
5	Goal setting
6	Home activities for next session
7	Group discussion
8	Summary and close
Session 4 (week 8)	Managing stress and emotions and the COPD action plan
1	Welcome back
2	Solution focused goal feedback
3	Managing stress and emotions
4	Action plans
5	Goal setting
6	Activities for next session
7	Summary and close
Session 5 (week 14)	Question and answer
1	Welcome back
2	Solution focused goal feedback
3	Question and answer
4	Goal setting
5	Activities for next session
6	Summary and close
Session 6 (week 20)	Keeping going from here
1	Welcome back
2	Solution focused goal feedback
3	Hobbies
4	Maintaining exercise
5	Sharing success
6	Summary and close

COPD, chronic obstructive pulmonary disease; SPACE for COPD(C), Self-Management Programme of Activity Coping and Education.

**Table 2 T2:** Taxonomy components present in the SPACE for COPD(C) facilitator manual, elaboration of the techniques under each component, direct examples from the SPACE for COPD(C) facilitator manual and the dose of the component

Taxonomy component	Elaboration	Examples from the SPACE for COPD(C) facilitator manual (*dose*)
A2. Information about available resources		Participants are provided with information throughout the programme (*every session*).
A3. Provision of/agreement on specific clinical action plans and/or rescue medication		*Session 4:* Action plans (*session 4 only*).
A6. Practical support with adherence (medication or behavioural)	Walking and strength training diaries are provided for participants and discussed during sessions.	Walking and strength training diaries are provided for participants and discussed during solution focused goal feedback at the beginning of sessions 3–6 (*sessions 3–6*).
A8. Safety netting	Participants are able to call programme facilitators between sessions if needed	Participants are provided with contact details for programme facilitators who they can call if needed (*this is a constant throughout the programme*).
A11. Training/rehearsal for practical self-management activities	Including: managing shortness of breath saving your energy	*Session 2:* Managing shortness of breath (*session 2 only*). *Session 3:* Saving your energy (*session 3 only*).
A12. Training/rehearsal in psychological strategies	Including: goal setting (including action planning) solution focused goal feedback problem solving self-reward and social reward managing stress and emotions	Goal setting activity (including action planning) and solution focused goal feedback (*once every session*). Problem solving (*this is a constant throughout the programme*). *Session 4:* Managing stress and emotions (*session 4 only*).
A13. Social support	Including: practical support emotional support	Participants are encouraged to share experiences, advice, ideas and support each other (*this is a constant throughout the programme*).
A14. Lifestyle advice and support	Including: introduction to the walking programme strength training hobbies maintaining exercise	*Session 2:* Introduction to the walking programme (*session 2 only*). *Session 3:* Strength training (*session 3 only*). *Session 6:* Hobbies (*session 6 only*). *Session 6:* Maintaining exercise (*session 6 only*).

SPACE for COPD(C), Self-management Programme of Activity Coping and Education.

Participants will also be asked to complete the exercise component of the manual at home in their own time. A full description of the rationale, development and efficacy of the work underpinning the SPACE for COPD(C) manual is detailed elsewhere.^9^ The intervention will be offered over a period of 2 years (the duration of the active component of the intervention within the study) and will only be offered as part of the research, not routine practice within the community.

### Intervention fidelity

Intervention facilitators are registered health professionals (physiotherapists, respiratory nurse specialists and health psychologists). In total, eight registered health professionals will be trained to deliver the SPACE for COPD(C) group-based intervention by two health psychologists.

All facilitators attended a 1-day training course to ensure that they understood the theories and philosophy underpinning the SPACE for COPD(C) group-based programme and the content and resources used within it. All facilitators were given a facilitator manual to support their delivery of the programme and given the opportunity to practise delivering at least one activity from the manual during the training session.

### Quality assurance

Quality assurance will be undertaken to assess delivery of intervention content and educational style. Intervention fidelity checklists for intervention facilitators and trained observers have been specifically designed for the study. Intervention facilitators will complete checklists at the end of each self-management group session, and one of the trainers will observe one session per self-management group, completing their own checklist. Intervention facilitators will receive written and verbal feedback from the trained assessor.

### Study outcomes

Data will be collected during baseline, 6-month and 9-month appointments at the Leicester Respiratory Biomedical Research Unit by trained members of the study team. Data are collected following standardised operating procedures. Written informed consent is obtained from all participants prior to the commencement of data collection. Details of all clinical assessments and outcome measures are provided in table 3. General practitioners are informed of patients’ participation in the trial and any relevant results. Any serious adverse events will be reported to the sponsor and patients’ ability to exercise safely will be monitored.

**Table 3 T3:** Details of study clinical assessments and outcome measures at all appointments

Baseline appointment (blinded and unblinded study team members)	6-month appointment (blinded study team member)	9-month appointment (blinded or unblinded study team member)
Consent Collection of demographic details and medical history Blood pressure Spirometry Randomisation* Questionnaires (CAT, EQ-5D, CRQ-SR, BCKQ, PAM, HADS)* Shuttle walking tests* (intervention participants only): 2xISWT; 1xESWT Participants given Senswear activity monitor to wear for 7 days*	Check consent Questionnaires (CAT, EQ-5D, CRQ-SR, BCKQ, PAM, HADS) Shuttle walking tests† Participants given Senswear activity monitor to wear for 7 days	Check consent Questionnaires (CAT, EQ-5D, CRQ-SR, BCKQ, PAM, HADS) Shuttle walking tests Participants given Senswear activity monitor to wear for 7 days

*Carried out by an unblinded member of the study team.

†ESWT carried out by an unblinded member of the study team.

BCKQ, Bristol COPD Knowledge Questionnaire; CAT, COPD Assessment Test; CRQ-SR, Chronic Respiratory Questionnaire; EQ-5D, European Quality of Life-5 Dimensions; ESWT, endurance shuttle walking test; ISWT, incremental shuttle walking test; HADS, Hospital Anxiety and Depression Questionnaire.; PAM, Patient Activation Measure.

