**Methods and analysis:**

A prospective, multi-site, single-blinded randomised controlled trial (RCT) will be conducted, with follow-up at 6 and 9 months. Participants will be randomly assigned to either the control group (usual care) or intervention group (a six-session, group-based SPACE for COPD(C)self-management programme delivered over 5 months). The primary outcome is change in COPD assessment test at 6 months.

A discussion session will be conducted with HCPs who deliver the intervention to discuss and gain insight into any potential facilitators/barriers to implementing the intervention in practice. Furthermore, we will conduct semi-structured focus groups with intervention participants to understand feasibility and acceptability. All qualitative data will be analysed thematically.

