## Methods/design

### Study design

The trial is a prospective, multi-site, single (assessor) blinded randomised controlled trial comparing a community-based, HCP-led, group-based self-management programme based on the SPACE for COPD(C) manual with usual care. The design of the study and flow of participants is described in figure 1. The study will be run across Leicestershire and Rutland, and a total of 150 participants will be recruited (75 in the intervention group and 75 in the control group).

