### Randomisation

Once participants have consented to take part in the study and spirometry has confirmed a COPD diagnosis, participants are randomised by an unblinded member of the study team using an online randomisation tool (sealed envelope).^14^ Individuals are randomised (1:1) to the control group or the intervention (SPACE for COPD(C) group-based self-management programme) group. The system randomises patients in random permuted blocks. This allows for the 1:1 ratio, but due to the random permuted blocks of 2, 4 or 6 ensures full randomisation. Simple randomisation has been chosen as there has been no requirement to stratify by age, gender, location or other variables. Participants are immediately informed of their allocated treatment by an unblinded member of the study team. Unblinding is permissible in the case of medical emergencies (eg, cardiac arrest) or patients being admitted to hospital for an exacerbation.

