### Primary outcome

The primary outcome is health status, as measured by the COPD Assessment Test (CAT)^16^ at 6 months post-baseline. This measure was chosen due to ease of use in clinical practice compared with the Chronic Respiratory Questionnaire (as used in the previous RCT). The CAT is a validated, short (eight items) and simple patient completed questionnaire and assesses globally the impact of COPD (cough, sputum, dyspnoea and chest tightness) on health status. The CAT is scored 0–5 with a range of 0–40; scores of 0–10, 11–20, 21–30, 31–40 represent mild, moderate, severe or very severe clinical impact, respectively.

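### The trial is labelled assessor-blinded without limit, but the plan guarantees a blinded assessor only at 6 months (except for the ESWT); the 9-month walk tests may be run by unblinded staff

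*Protocol article*

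**What the plan says.** The Study design section of the protocol article states: "The trial is a prospective, multi-site, single (assessor) blinded randomised controlled trial". The Methods and analysis paragraph of the abstract uses the same label and names both follow-up visits under it: "single-blinded randomised controlled trial (RCT) will be conducted, with follow-up at 6 and 9 months". Neither statement excepts a visit or a test.

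Table 3, under Study outcomes, gives the assessor visit by visit. The middle column is headed "6-month appointment (blinded study team member", with a footnote to the shuttle tests: "ESWT carried out by an unblinded member of the study team". The last column is headed "9-month appointment (blinded or unblinded study team member". The items listed at 9 months are the same as at 6 months: six questionnaires, the shuttle walking tests and the activity monitor.

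The Randomisation section says "Participants are immediately informed of their allocated treatment by an unblinded member of the study team". It allows unblinding for medical emergencies and for hospital admission with an exacerbation, and gives no other reason.

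**The concern.** The design statement claims a property that the visit schedule does not secure. Routine use of unblinded staff at 9 months fits neither reason for unblinding given under Randomisation. Nothing in the article says when such staff may be used, how their use is kept even between the arms, or that the blinding claim was meant for 6 months only.

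The strengths and limitations box places the end of follow-up 3 months after the intervention. The 9-month visit is therefore the planned look at whether any benefit lasts once the programme has stopped. A walk test is run by a member of staff, whose encouragement and judgement of when the test has ended can shift with knowledge of the arm. If 6-month tests are blinded and some 9-month tests are not, a change between the two visits could reflect the assessor as well as the patient. A reader who trusts the label would credit the 9-month walk results with a protection that the plan does not promise.

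**Working it through.** The point concerns who assesses what and rests on no figure in the plan, so the check is to set the statements side by side.

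**Step 1: label against schedule**

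| Source | Time point | Assessor |
|---|---|---|
| Study design; abstract | no visit excepted | blinded |
| Table 3 | 6 months, all items but the ESWT | blinded |
| Table 3, footnote | 6 months, ESWT | unblinded |
| Table 3 | 9 months, all items | either, no rule given |

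The label and the schedule agree only in the second row.

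**Step 2: where assessor blinding could matter**

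Table 3 lists six questionnaires (CAT, EQ-5D, CRQ-SR, BCKQ, PAM, HADS) and one body-worn activity monitor at each follow-up visit. The section on exercise capacity names two shuttle tests, the ISWT and the ESWT. That makes 6 + 1 + 2 = 9 instruments per visit.

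- Questionnaires (6 of 9): answered by participants who know their allocation. Blinding the staff member adds little beyond guarding against influence while the forms are completed.
- Activity monitor (1 of 9): recorded by the device over the week after the visit.
- Walk tests (2 of 9): conducted by staff. This is where blinding the assessor can do most.

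At 6 months, one of the two walk tests (the ISWT) is covered and the other (the ESWT) is not. At 9 months, neither is guaranteed.

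**Step 3: the primary outcome**

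Health status is taken at 6 months, "as measured by the COPD Assessment Test (CAT") and described as a "simple patient completed questionnaire". Table 3 puts that assessment at the blinded visit, so the 9-month wording does not reach it.

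**Step 4: whether there is a two-arm walk comparison**

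Table 3 restricts the baseline shuttle tests to the intervention arm. The follow-up columns carry no such restriction, but they do not say that controls walk either. If controls walk at follow-up, a between-arm comparison without a control baseline rests on follow-up values alone, and unbiased assessment matters all the more. If they do not, there is no between-arm walk comparison for an unblinded assessor to distort.

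**The case against.** The strongest reply is that nothing is hidden. Table 3 gives the blinding status for each visit, and a footnote flags the ESWT. Securing blinding at the primary time point and allowing flexibility at a secondary visit is a defensible choice. The Study outcomes section also refers to trained staff and standardised operating procedures, and the ISWT follows a published protocol.

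Much of this stands. The disclosure in Table 3 is why the point concerns an unqualified label and a missing rule, not concealment. Standard procedures reduce the room for differential encouragement, but they do not replace blinding, and the general label still says more than the table supports. The 6-month ESWT exception may even be a way to protect the blinded assessor, if only one arm does that test, but the article does not say so.

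Three stronger readings are tempting and are not supported:

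- A reader might infer that all walk tests lack blinding. The 6-month ISWT is at the blinded visit, and the footnote exempts only the ESWT.
- A reader might infer that every 9-month outcome loses its protection. Most are self-reported by participants who know their arm or are recorded by a device, so assessor blinding offered them little to begin with.
- A reader might infer that 9-month assessments will be unblinded. Table 3 permits this and does not require it; the protection is not guaranteed, which is different from absent.

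**Conclusion.** The point holds in a limited form. The blinding claim is broader than the schedule, and the plan guarantees a blinded assessor only at 6 months, without the ESWT. The 6-month CAT assessment and the 6-month ISWT are not affected. The exposure is mainly the ISWT and ESWT at 9 months, together with the ESWT at 6 months, all of them secondary outcomes. It exists only so far as both arms perform these tests, which the article leaves open.

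No size in metres can be given. The documents contain no estimate of how far an assessor who knows the arm shifts walking distance. A reader might be inclined to set an assumed shift against the 47.5 m quoted for the ISWT, but that figure is a threshold for change in an individual and does not measure bias in a difference between groups. The share of 9-month visits done unblinded is also unknown and could lie anywhere from none to all.

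**What to change.** 1. Have the blinded assessors who already run the 6-month visits conduct at least the 9-month ISWT. The cost is a small loss of scheduling flexibility, assuming those staff are available at 9 months, which the article does not state.
2. Where this cannot be done, record the assessor's blinding status at each visit, which needs one field on the case report form, and report it by arm.
3. In that case, also limit the claim in the abstract and the Study design section to assessor-blinded at 6 months except for the ESWT, and do not present the 9-month walk results as blinded. The cost is a less favourable blinding statement.

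An analysis restricted to blinded 9-month assessments should be descriptive at most. Assessor status is not randomised and arises after randomisation. Because unblinding is allowed on admission for an exacerbation, that subset could leave out sicker patients.

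The protocol version note gives a study end of 06/2017 and reports recruitment in the past tense. If the visits are already over, the first step is no longer possible; the wording change remains, as does reporting by arm where assessor status was recorded or can be recovered.

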### Data analysis

#### Study power

The power calculation was based on the primary outcome at 6 months.^30 31^ To detect a mean±SD between-group difference of 2.5±5.0 in the change in CAT with 80% power, 60 people per group are required (α=0.05, two tailed). In anticipation of a possible 25% attrition rate, the total sample size was increased to 75 per group (150 in total).

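### As listed, the baseline CAT appears to be completed after randomisation and disclosure, so the change in CAT could carry a reaction to the allocation

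*Protocol article*

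**What the plan says.** Table 3 (Study outcomes) lists the baseline appointment as consent, demographics and history, blood pressure, and then "Spirometry Randomisation* Questionnaires (CAT, EQ-5D, CRQ-SR, BCKQ, PAM, HADS". Next come "Shuttle walking tests* (intervention participants only): 2xISWT; 1xESWT" and the activity monitor. The asterisk on randomisation, and on every item after it, means "Carried out by an unblinded member of the study team". Nothing before randomisation carries it. The column heading shows that both blinded and unblinded team members take part in this visit.

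The Randomisation section gives the trigger: "Once participants have consented to take part in the study and spirometry has confirmed a COPD diagnosis, participants are randomised by an unblinded member". It continues: "Participants are immediately informed of their allocated treatment by an unblinded member of the study team".

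On the endpoint, the abstract says "The primary outcome is change in COPD assessment test at 6 months", and Study power sizes the trial on a "between-group difference of 2.5±5.0 in the change in CAT". The Primary outcome section words it differently: "The primary outcome is health status, as measured by the COPD Assessment Test (CAT", taken at 6 months after baseline. It also describes the CAT as completed by the patient. Quantitative analysis plans to adjust for baseline differences without naming a model. The trial is blinded at assessor level only.

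**The concern.** A baseline value is protected by randomisation only if it is recorded before the allocation can influence it. If patients answer the CAT just after learning their arm, some may rate themselves differently because of what they were told, for example from relief, from disappointment or to justify a need for help. Higher CAT scores mean worse health. If controls score worse on hearing the news, their later change looks better than it is and a real benefit is hidden. If intervention patients score worse, a benefit can appear where there is none.

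The primary outcome is affected because the baseline CAT is one half of the change score. The baseline EQ-5D, CRQ-SR, BCKQ, PAM and HADS stand in the same place in the list and share the exposure. The use of unblinded staff matters less, since the patient is the rater.

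**Working it through.** **Step 1: the order of events.** Table 3 does not say that its list is chronological. Four facts bear on it.

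- The conditions for randomisation in the Randomisation section (consent, spirometry) are listed before it in Table 3. Completed questionnaires are not among them.
- The baseline walking tests are for the intervention arm only, so allocation is known before the visit's procedures end.
- The unblinded-staff mark starts at randomisation and covers everything after it, including the questionnaires. This fits a handover at that point. Questionnaires done before allocation would not need unblinded staff.
- No section places the baseline CAT before randomisation.

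The natural reading is randomise, disclose, then questionnaires.

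**Step 2: how a shift reaches the result.** Let *s* be the difference between arms in baseline CAT caused by disclosure, and *p* the fraction of it still present at 6 months.

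- Change score: bias = (1 − *p*) × *s* in absolute size. If the reaction has faded (*p* = 0), the bias is *s*. If it persists in full (*p* = 1), it cancels.
- Baseline-adjusted analysis with slope *b*, at *p* = 0: bias = *b* × *s*.
- 6-month CAT with no baseline: the baseline reaction does not enter.

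**Step 3: the plan's own figure.** Inputs from Study power: difference 2.5, SD 5.0, two-sided α 0.05, power 80%, stated n = 60 per group.

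- Normal approximation: n = 2 × (1.960 + 0.842)² × (5.0/2.5)² = 62.8, so 63 per group; the t-test gives 64.
- At 60 per group, t-test power is 77.5%. This is the reference below. The gap from 80% is a separate matter.

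**Step 4: illustration for the change score.** SE = 5.0 × √(2/60) = 0.913; noncentral t with 118 degrees of freedom; *p* = 0. The values of *s* are assumed.

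| *s* (points) | Share of 2.5 target | *s*/SE | Type I error, no true effect | Power for 2.5 if the shift opposes it |
|---|---|---|---|---|
| 0 | 0% | 0 | 5.0% | 77.5% |
| 0.5 | 20% | 0.55 | 8.4% | 58.4% |
| 1.0 | 40% | 1.10 | 19.2% | 37.1% |

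**Step 5: illustration with baseline adjustment.** Take *s* = 1.0 and slopes 0.5 to 0.7 (assumed), so the bias is 0.5 to 0.7 points.

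- If the variance is equal at baseline and 6 months, the slope equals the correlation and the residual SD is 5.0 × √((1 + *b*)/2), i.e. 4.33 to 4.61. Type I error is then 9.6% to 13.1%.
- With the residual SD left at 5.0, it is 8.4% to 11.8%.

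Adjustment reduces the bias but does not remove it.

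**The case against.** The strongest objection is that the sequence is inferred. Table 3 is a list of contents. The intervention-only walking tests show that randomisation precedes those tests, not that it precedes the questionnaires. The stated conditions for randomisation do not rule out other steps coming first, and the operating procedures that govern data collection are not shown. This stands as a limit on certainty. It does not overturn the reading, because the placing of the unblinded-staff mark supports that order and nothing in the article contradicts it.

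Second, full pass-through needs a reaction that is present at baseline and gone by 6 months. Patients know their arm at both visits, and a lasting reporting tendency would partly or wholly cancel in a change score. This stands, and the illustration depends on it.

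Third, the sizes are assumed, and the article gives no evidence that any shift occurred. This also stands.

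Fourth, under the Primary outcome section's wording, an unadjusted comparison of 6-month CAT would not use the baseline at all. But the abstract and the power calculation use change, and adjustment for baseline differences is planned.

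A reader might go further and infer that the damage is irreparable. It is not: a comparison of 6-month CAT without the baseline is free of this particular bias. Nor do the documents support saying that controls are told they will receive nothing, since they continue with usual care and reviews. The idea that disappointed controls leave before completing the baseline CAT is speculation.

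**Conclusion.** The point holds as a design weakness in the document as written. The baseline CAT appears to be collected after the patient knows the arm, and it forms part of the change on which the trial is powered. An arm-specific reaction that fades by 6 months would bias the change score by its full size and a baseline-adjusted result by part of it. Assumed shifts of 0.5 and 1.0 points would give type I errors of 8.4% and 19.2%, or power of 58.4% and 37.1% against 77.5%. These figures rest on 60 analysed per arm, SD 5.0, a fully transient reaction and invented shift sizes.

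They show sensitivity, not that the trial is biased. A reader might conclude that bias has been demonstrated or that its direction is known; the documents support neither. The point should be fixed, with moderate to high confidence.

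**What to change.** 1. In Table 3, list the CAT and the other questionnaires after spirometry and before randomisation, collected by the blinded team member already named for that visit. In the Randomisation section, state that randomisation and disclosure follow their completion. This can apply only to participants not yet randomised. The Protocol version section gives a February 2015 start and describes recruitment in the past tense, so few or none may benefit. If practice was already questionnaires first, correct both places to say so.

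2. For participants randomised under the listed order, specify a sensitivity analysis comparing 6-month CAT between arms without the post-disclosure baseline. It removes this bias, but not any reporting effect at 6 months from patients knowing their arm.

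**Cost.** Re-ordering needs no extra visit, form or sample size; a few people may complete questionnaires and then not be randomised. The sensitivity analysis costs some precision. With equal variances, the SD of 6-month CAT is 5.0/√(2(1 − *r*)): 5.0 at an assumed correlation *r* = 0.5 and 6.45 at 0.7, against 5.0 for the change and 4.33 to 4.61 after baseline adjustment.

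### As written, the baseline visit takes the CAT after randomisation and disclosure of the arm, which leaves the baseline half of the primary change score open to allocation-related reporting bias

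*Protocol article*

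**What the plan says.** Table 3 in Study outcomes gives the baseline visit as consent, demographics and history, blood pressure and spirometry, followed by "Randomisation* Questionnaires (CAT, EQ-5D, CRQ-SR, BCKQ, PAM, HADS", then the shuttle walks and the activity monitor. Randomisation and every item after it carry an asterisk, explained as "Carried out by an unblinded member of the study team". No earlier item carries it. The walking tests are listed as "Shuttle walking tests* (intervention participants only): 2xISWT; 1xESWT".

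The Randomisation section names two conditions for allocation: "Once participants have consented to take part in the study and spirometry has confirmed a COPD diagnosis, participants are randomised by an unblinded member". It then says: "Participants are immediately informed of their allocated treatment by an unblinded member of the study team".

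The abstract states: "The primary outcome is change in COPD assessment test at 6 months". Study power is also based on the change in CAT (2.5 points, SD 5.0). Primary outcome words it differently, as CAT at 6 months after baseline, and describes the instrument as a "simple patient completed questionnaire". Study design calls the trial a "single (assessor) blinded randomised controlled trial", and Table 3 gives the 6-month visit to a blinded team member. Quantitative analysis promises to adjust for any baseline differences.

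**The concern.** A change score, or an adjustment for baseline, relies on a baseline that allocation cannot have influenced. The CAT is self-reported. A patient who has just heard that they will receive usual care, or the programme, may answer differently for that reason alone. A between-arm difference produced in this way enters the change score although it has nothing to do with the effect of treatment.

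The planned adjustment is not a safeguard, because it would use the same post-allocation measurement. The EQ-5D, CRQ-SR, BCKQ, PAM and HADS are in the same position. The first activity recording is too, since the monitor is handed out after randomisation and worn for the following seven days.

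**Working it through.** **Step 1: is the order really randomisation first?** No sentence states when the questionnaires are completed, so the order has to be read from four features:
- Table 3 lists randomisation before the questionnaires.
- The asterisk for unblinded staff begins exactly at randomisation and covers everything after it, as a handover at that point would.
- The baseline walks are for one arm only, so allocation is known before the visit ends.
- The Randomisation section makes consent and spirometry the conditions for allocation, does not mention the questionnaires, and has patients told at once.

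Nothing in the article puts the questionnaires before randomisation.

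**Step 2: the plan's own figure.** Inputs from Study power: difference 2.5, SD 5.0, two-sided alpha 0.05, power 80%.
- n = 2 × (1.960 + 0.842)² × (5.0/2.5)² = 62.8, so 63 per group, against 60 stated.
- With 60 per group, SE = 5.0 × √(2/60) = 0.913 and power is 78.2%.

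The gap between 60 and 63 is a separate matter. The stated 60 per group is used below.

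**Step 3: bias in the change score.** Let b be the between-arm reporting shift in baseline CAT caused by knowing the arm, and k the fraction of it still present at 6 months (0 to 1). Both are assumptions. The size of the bias is (1 − k) × b.
- k = 0 (shift gone by 6 months): b = 0.5 gives 0.5, and 0.5/2.5 = 20% of the target. b = 1.0 gives 1.0, and 1.0/2.5 = 40%.
- k = 0.5: the bias is 0.25 to 0.5 point, 10% to 20% of the target.
- k = 1: the shift cancels.

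**Step 4: error rates at k = 0, normal approximation, SE 0.913.**

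| Assumed b | Type I error, no true effect | Power for a true 2.5, shift against the intervention |
|---|---|---|
| 0 | 5% | 78.2% |
| 0.5 | 8.5% | 59.1% |
| 1.0 | 19.5% | 37.6% |

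A shift in the other direction would inflate the apparent effect instead.

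**Step 5: bias after adjusting for the same baseline.** With regression slope s of 6-month CAT on baseline, the bias is (k − s) × b. At k = 0 and an assumed s of 0.7, its size is 0.7 × 0.5 = 0.35 to 0.7 × 1.0 = 0.7 point. Adjustment removes the bias only if k happens to equal s.

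**The case against.** The strongest reply is that the order is inferred. Table 3 is a list of assessments and outcome measures, not a timed schedule. The asterisk says who does an item, not when, and the arm-specific walks show only that the walks follow allocation. This stands as a limit on certainty. It does not reverse the reading, because every indication points the same way and none points the other. It does mean that the remedy must allow for the table being wrong about practice.

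A reader might infer that the baseline has in fact been contaminated, or that any baseline shift passes in full into the primary result. The documents support neither. They contain no evidence that a shift occurred, and the full effect requires that it has gone by 6 months. Patients know their arm throughout, so part of a reporting shift may persist and cancel in the change score.

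The wording under Primary outcome also matters: a plain between-arm comparison of 6-month CAT does not use the baseline and would be untouched by a baseline shift. The exposure applies to the change-score definition in the abstract and in Study power.

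Finally, because patients complete the CAT themselves, the staff member's knowledge of the arm matters less than the patient's own.

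**Conclusion.** The point holds as an avoidable weakness in how the baseline visit is laid out. As written, the baseline CAT follows disclosure, so the primary change score is open to allocation-related reporting bias that adjustment for the same baseline would not reliably remove.

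Its size and direction are unknown. Under an assumed transient shift of 0.5 to 1.0 point, the bias is 20% to 40% of the 2.5-point target for a change score, and 0.35 to 0.7 point after adjustment with an assumed slope of 0.7. The change-score bias is smaller if the shift persists to 6 months. The conclusion rests on reading Table 3 as the order of procedures and on change in CAT being the primary analysis.

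**What to change.** **Order of the visit.** Complete the CAT and all other baseline questionnaires after consent and spirometry but before randomisation and disclosure. The blinded team member already listed for the baseline visit can give them. If this is what happens, correct Table 3 and the Randomisation section to say so. The change reorders steps within one visit and needs no extra visit, measurement or participants.

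**Participants already enrolled.** The Protocol version section gives a start in 02/2015 and refers to recruitment in the past tense, so reordering may come too late for many or all of them. For anyone enrolled under the listed order, report baseline CAT by arm and add a between-arm comparison of 6-month CAT that does not use the baseline. The cost is precision. If the SD is equal at both visits and the correlation is 0.7 (assumed), the 6-month SD implied by a change SD of 5.0 is 5.0/√(2 × 0.3) = 6.45. The SE with 60 per group is then 6.45 × √(2/60) = 1.18, against 0.913 for the change score.

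**Activity monitor.** Treat the first 7-day recording as post-randomisation, and do not use it as a covariate or as the origin of a change score. Delaying randomisation until the monitor is returned is not recommended. The baseline walks depend on the arm, so intervention participants could need a second baseline visit.
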